## Abstract

**Background:**

Anterior open treatment of the inguinal hernia with a tension free mesh has reduced the incidence of recurrence and direct postoperative pain. The Lichtenstein procedure rules nowadays as reference technique for hernia treatment. Not recurrences but chronic pain is the main postoperative complication in inguinal hernia repair after Lichtenstein's technique. Preliminary experiences with a soft mesh placed in the preperitoneal space showed good results and less chronic pain.

**Methods:**

The TULIP is a double-blind randomised controlled trial in which 300 patients will be randomly allocated to anterior inguinal hernia repair according to Lichtenstein or the transinguinal preperitoneal technique with soft mesh. All unilateral primary inguinal hernia patients eligible for operation who meet inclusion criteria will be invited to participate in this trial. The primary endpoint will be direct postoperative- and chronic pain. Secondary endpoints are operation time, postoperative complications, hospital stay, costs, return to daily activities (e.g. work) and recurrence. Both groups will be evaluated.

Success rate of hernia repair and complications will be measured as safeguard for quality.

To demonstrate that inguinal hernia repair according to the transinguinal preperitoneal (TIPP) technique reduces postoperative pain to <10%, with α = 0,05 and power 80%, a total sample size of 300 patients was calculated.

**Discussion:**

The TULIP trial is aimed to show a reduction in postoperative chronic pain after anterior hernia repair according to the transinguinal preperitoneal (TIPP) technique, compared to Lichtenstein.

In our hypothesis the TIPP technique reduces chronic pain compared to Lichtenstein.

**Trial registration:**

ISRCTN 93798494

## Background

Inguinal hernia is a common surgical problem. In the Netherlands more than 26.000 unilateral inguinal hernia repairs are performed each year [1]. Tension free mesh repair has reduced the incidence of recurrence and direct post operative pain. The incidence of recurrences are 2-5% [2]. However, chronic pain after inguinal hernia repair is an underestimated problem [3].

The exact incidence of chronic pain is unknown. Well conducted, large and unselected epidemiological studies suggest that about 20% of patients are affected with chronic pain [4-7]. A randomised controlled trial comparing Shouldice, Lichtenstein and endoscopic preperitoneal repair showed that 31% of patients had some form of chronic pain after Lichtenstein repair [8]. Patients are classified as having chronic pain if postoperative pain lasts for more than three months [9]. Chronic pain may vary from subtle discomfort to disabling pain. In general, three chronic groin pain syndromes have been defined: somatic, neuropathic, and visceral pain [10]. Somatic pain is localized to the pubic tubercle and is a result of periosteal damage during stapling of prosthetic mesh or incorporation of the peri-osteum into the most medial stitch of an open anterior repair. Neuropathic pain usually develops in the sensory distribution of the injured nerve and can present days to weeks after the repair. Chronic neuralgia results from nerve trauma secondary to partial or complete division, stretching, contusion, crushing, electrical damage, suture compression, and adjacent inflammation from mesh or suture material [11,12]. The most commonly offended nerves after open inguinal hernia repair include the ilioinguinal-, iliohypogastric-, and genital branch of the genitofemoral nerve [13]. Visceral pain usually presents as chronic orchalgia, or pain during ejaculation, and can be a result of stricture of the spermatic duct or damage to the somatic sacral or sympathetic nerves [14].

To assess the objectivity of pain the visual analogue scale (VAS score) is frequently used nowadays [15]. VAS has been a proven instrument to score postoperative pain in inguinal surgery. Chronic pain has significant effects on all daily activities including walking, work, sleep, relationships with other people, mood and general enjoyment of life [16]. So much effort has been put in strategies to reduce chronic pain.

Endoscopic hernia repair has been postulated to result in less chronic pain due to the preperitoneal placed position of the mesh.

Several studies have been performed to investigate if endoscopic repair resulted in less chronic pain. A large mesh is placed in preperitoneal position to cover the myopectineal orifice after reduction of the hernia sac. Liem et al. concluded a lower incidence of pain after endoscopic hernia repair compared to open non-mesh repair [17]. Grant et al. however found in a randomised trial after 5 years that the incidence of chronic pain was still 27% at one year compared with 36% chronic pain in the Lichtenstein group. Groin numbness was significantly reduced (18% vs 40%) [18]. Specialized hernia centres reported excellent results after endoscopic repair. Wright failed to prove reduced pain after endoscopic approach (13% vs. 10%) in a randomised controlled trial with 5 years follow up. This study showed that testicular pain was more frequent after endoscopic repair and groin pain more common after open repair [19]. A review of randomised controlled trials comparing endoscopic with open mesh hernia repair showed that the endoscopic approach was associated with less persisting pain [2].

The drawback of endoscopic hernia repair over the open approach is the added costs, particularly when disposable instruments are used [20]. The other disadvantage of laparoscopy compared with open hernia repair is that general anaesthesia is necessary. Finally, the endoscopic learning curve is long [21]. The principal reasons for the long learning curve are the surgeon's lack of familiarity with the preperitoneal anatomy and the time it takes to develop the skills to operate in a confined space. Complications of endoscopic hernia repair are scarce but might be severe.

One study prospectively investigated the incidence of pain after inguinal hernia correction under local anaesthesia. Some form of pain was reported by 19% of patients and severe pain by 6% of patients after one year [22].

Other meshes have been developed and tested to reduce the chronic pain after inguinal hernia repair. A randomised clinical trial comparing the Prolene Hernia System, mesh plug repair and Lichtenstein method for open inguinal hernia repair showed that 39,7% of patients had some form of pain after three months. No difference could be detected between type of mesh used [23].

### Rationale for the soft mesh

No recent systematic review or meta-analysis regarding postoperative pain after inguinal hernia repair has been performed.

Endoscopic preperitoneal approach in order to reduce pain is expensive and has several other disadvantages, but a cost-effectiveness meta analysis has to be performed yet.

Since pain is often related to neuralgia and recurrences occur at the myopectineal orifice an alternative mesh was developed to be placed in the preperitoneal space, but with anterior approach. Preliminary experience with a preperitoneal placed mesh of 8-10 cm long and 6-7 cm wide in 116 patients showed a recurrence rate of 0,7% with a median follow up of 63 months [24]. After adding a memory ring to the mesh to allow easy placement in the preperitoneal space, preliminary results in 126 patients with a median follow up of 24 months show a recurrence rate of 1,6% and reported pain in 5,6% of patients [25]. A prospective study on feasibility and postoperative outcome of this memory ring-equipped-mesh showed that this method could be achieved in all 200 patients and with a low risk of postoperative complications (7% benign, of which 10 patients complained of mild pain postoperatively) [26].

The transinguinal preperitoneal (TIPP) technique with soft mesh combines the anterior approach according to Lichtenstein with the preperitoneal position of the mesh as known from the endoscopic total extra peritoneal technique (TEP).

This paper describes the rationale of this product and the design of the study.

## Methods

### Study objectives

Two techniques, Lichtenstein and TIPP, for inguinal hernia patients will be compared in a prospective randomised double blind clinical trial. Patients will be included at the outpatient departments of both hospitals by surgeons and supervised residents. Dedicated hernia surgeons will always supervise and/or perform the operations.

Objective success: the percentage of operations with successful inguinal hernia reduction and direct postoperative - and chronic pain incidence lower than 25%.

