### Primary endpoint

The primary endpoint is the incidence of direct postoperative pain and chronic pain after inguinal hernia repair according to Lichtenstein or TIPP using the visual analogue scale (VAS).

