### Statistical analysis

The analysis will be performed on the basis of intention-to-treat principles.

It is anticipated that the use of TIPP technique with soft mesh at least will lead to a reduction in postoperative chronic pain from 25% to 10%. The sample size calculation is based on α = 0,05 and a power of 80%. This leads to a required sample size of 300 patients. Taking into account a 5% loss-to-follow up, a total of 2 × 158 patients will be randomized. There are three postoperative follow up visits at the outpatient department at two weeks, three months and one year for both groups (Lichtenstein and TIPP). The expected study end is December of 2010 (after 1,5 years inclusion period).

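### The success definition under Study objectives is an absolute pain cut-off set at the assumed Lichtenstein rate, so it does not test whether TIPP is better than Lichtenstein

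*Protocol article*

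**What the plan says.** All places are in the protocol article.

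- **Study objectives:** the two techniques are to be compared. Success is then defined as the percentage of operations with a successful reduction and "direct postoperative - and chronic pain incidence lower than 25" per cent. The definition names no arm, comparator, visit or test.
- **Abstract, Discussion:** the hypothesis is comparative: "In our hypothesis the TIPP technique reduces chronic pain compared to Lichtenstein".
- **Primary endpoint:** there are two components: "The primary endpoint is the incidence of direct postoperative pain and chronic pain after inguinal hernia repair", measured by VAS in both procedures.
- **Statistical analysis:** the trial is sized on a "reduction in postoperative chronic pain from 25% to 10" per cent, presented as the least that TIPP should achieve. "The sample size calculation is based on α = 0,05 and a power of 80" per cent, and "This leads to a required sample size of 300 patients". Sidedness is not given.
- **Abstract, Methods:** the same alpha, power and total appear with a shorter aim, that TIPP "reduces postoperative pain to <10" per cent. The same section says that repair success and complications are recorded to guard quality.

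No section says how the 25% cut-off relates to the comparison between arms.

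**The concern.** The only statement labelled as success under the study objectives uses a figure that is also the planning rate before any TIPP benefit. A TIPP arm that does no better than Lichtenstein can meet it. A TIPP arm that does clearly better can miss it if pain is commoner in this population than was assumed.

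If the report applies this definition as written, the trial could be called a success or a failure for reasons unrelated to the randomised contrast. If it is left beside the comparative hypothesis, there are two candidate answers and nothing fixed in advance to choose between them.

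**Working it through.** **Inputs.** The assumed chronic pain rates are 25% (Lichtenstein) and 10% (TIPP), with alpha 0.05, power 80% and a total of 300 (Statistical analysis). The TIPP arm has 150 patients (Surgical Techniques). The Background also cites chronic pain of about 20% in epidemiological studies, 31% after Lichtenstein in one randomised trial, and 36% in the Lichtenstein group of another. No rate for direct postoperative pain is given.

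**1. The plan's own figure.** For a two-sided comparison of two proportions, with mean rate 0.175 and difference 0.15:

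n per arm = [1.960·√(2·0.175·0.825) + 0.842·√(0.25·0.75 + 0.10·0.90)]² / 0.15² = (1.053 + 0.443)² / 0.0225 ≈ 100

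That is 200 in total, or 226 with continuity correction. The stated 300 is not reproduced; 150 per arm gives about 93% two-sided power for 25% versus 10%. This is a separate matter. It matters here only because the calculation is a between-arm one and I take 150 per arm as stated.

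**2. Chance of meeting the cut-off on chronic pain alone.** With n = 150, an observed rate below 25% means at most 37 patients with pain (37/150 = 24.7%; 38/150 = 25.3%). The chance is P(X ≤ 37) for X ~ Binomial(150, p):

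| True TIPP rate p | Source of the rate | P(observed < 25%) |
|---|---|---|
| 20% | epidemiological studies | 0.934 |
| 25% | planning rate, no benefit | 0.506 |
| 31% | Lichtenstein, one trial | 0.054 |
| 36% | Lichtenstein, another trial | 0.002 |

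At p = 25% the result hardly moves with the number analysed: 0.487 with n = 143 and 0.506 with n = 158. For comparison, a two-sided 5% test between arms would wrongly favour TIPP about 2.5% of the time when the arms do not differ.

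**3. The full rule.** Direct postoperative pain must also be below 25% and the reduction must succeed, so the joint chance cannot exceed the chronic-pain figure. As an illustration only, assume that direct pain also has a true rate of 25%. The normal approximation 0.25 + arcsin(ρ)/(2π) then gives 0.25 for independent components (ρ = 0) and 0.50 for fully correlated ones (ρ = 1). The actual joint chance cannot be computed from the document.

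**4. Conflict with the comparison.** Two possible chronic-pain results with 150 per arm:

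- TIPP 36/150 (24.0%), Lichtenstein 20/150 (13.3%). The cut-off is met, yet TIPP is worse: Fisher exact p = 0.026. The difference is +10.7 points, with standard error √(0.24·0.76/150 + 0.133·0.867/150) = 0.0446 and 95% CI about +1.9 to +19.4.
- TIPP 39/150 (26.0%), Lichtenstein 60/150 (40.0%). The cut-off is missed, yet TIPP is better: p = 0.014. The difference is −14.0 points, with standard error √(0.26·0.74/150 + 0.40·0.60/150) = 0.0537 and 95% CI about −24.5 to −3.5.

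**The case against.** The strongest reply is that the trial question is already comparative. Study objectives itself says that the techniques will be compared, the hypothesis is stated against Lichtenstein, and the sample size rests on a difference between arms. The success sentence names neither TIPP nor a test, and it is not the primary endpoint. It could be the quality safeguard mentioned in the Abstract. This stands in part: applying the cut-off to the TIPP arm is an interpretation. But the safeguard sentence does not mention 25%, nothing labels the definition as descriptive, and it is the only definition of success under the objectives. Even on the opposing reading, an absolute threshold at the control rate cannot show benefit.

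A second reply is that about half is a selective figure. That also stands. It covers one component, at one assumed rate, and is far lower at the Lichtenstein-specific rates that the document cites. For that reason the whole range is shown.

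A reader might also infer a three-way contradiction, with the below-10% aim in the Abstract as a further rule of its own. The document does not support this. That sentence carries the same alpha, power and total as the Statistical analysis section, where 10% is put as the least improvement expected. It is a loose shortening of the same calculation, and calculations that treat it as a one-sample test would assess a rule that the document does not clearly set.

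Finally, test details are commonly left to a fuller document. The point here is a criterion that the article does state, not one that it omits.

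**Conclusion.** The point holds for the definition under Study objectives. As written, it is an absolute cut-off at the assumed Lichtenstein rate and does not test the comparative hypothesis. On chronic pain alone, with 150 per arm and a true rate of 25%, a TIPP arm without benefit meets it about 51% of the time. At that rate this is roughly a ceiling for the joint rule. Over the background rates cited in the document the chance runs from 93% to 0.2%, so the rule measures how common pain is in the population and not the treatment effect.

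These figures assume that the cut-off is applied to the observed TIPP rate, which the text does not spell out. It would go too far to say that the full rule passes a useless technique half the time, because direct pain and successful reduction are also required and no direct-pain rate is given.

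**What to change.** **Study objectives.** Replace the 25% criterion with a between-arm one: a lower incidence of chronic pain with TIPP than with Lichtenstein at one follow-up visit named in advance, tested at the stated alpha of 0.05 with sidedness stated, and reported as a risk difference with 95% CI. The investigators must choose the visit and the sidedness. The article has visits at three months and one year, defines chronic pain as lasting more than three months, and does not settle either choice.

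**Primary endpoint.** Keep direct postoperative pain as the other stated component and compare it between arms too.

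**Planning figures and quality.** Keep 25% and 10% only as planning assumptions. Report successful reduction as the quality safeguard that the Abstract already names.

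**Minor alignment.** In the Abstract, reword the aim as a reduction in chronic pain from 25% to 10%, to match the Statistical analysis section.

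**Cost.** The wording of Study objectives and one sentence of the Abstract change; data collection and recruitment do not. The downside is that an absolute pain target is no longer part of the success definition. The observed incidence in each arm can still be reported.

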### Primary endpoint

The primary endpoint is the incidence of direct postoperative pain and chronic pain after inguinal hernia repair according to Lichtenstein or TIPP using the visual analogue scale (VAS).

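### The primary endpoint joins direct postoperative pain and chronic pain, but the single α of 0.05 and the 80% power are set for chronic pain only

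*Protocol article*

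**What the plan says.** The Primary endpoint section of the protocol article states: "The primary endpoint is the incidence of direct postoperative pain and chronic pain after inguinal hernia repair", measured by visual analogue scale. The abstract's Methods paragraph says the same: "The primary endpoint will be direct postoperative- and chronic pain".

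The Background classifies pain as chronic when it lasts more than three months, so the two parts are different outcomes. Pain is recorded at "three postoperative follow up visits at the outpatient department at two weeks, three months and one year for both groups".

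The design calculation covers one part. The Statistical analysis section anticipates a "reduction in postoperative chronic pain from 25% to 10" per cent, and adds: "The sample size calculation is based on α = 0,05 and a power of 80" per cent. It derives 300 patients, raised to 2 × 158 for 5% loss to follow-up. No rate or effect for direct postoperative pain appears anywhere in the article.

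The stated aim varies between sections:

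- Abstract, Discussion: chronic pain only ("In our hypothesis the TIPP technique reduces chronic pain compared to Lichtenstein").
- Abstract, Methods: the sample size is tied to postoperative pain in general ("technique reduces postoperative pain to <10%, with α = 0,05 and power 80%, a total sample size of 300 patients was calculated").
- Conclusion: the aim is a reduction in both kinds of pain.
- Study objectives: success requires hernia reduction and an incidence of direct and chronic pain below 25%. This is an absolute threshold, not a rule for comparing the arms.

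**The concern.** A primary endpoint, its α and its sample size should describe one decision. Here the endpoint has two parts and the calculation has one. Two readings are open, and the stated error rate and power do not both survive under either.

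- **Either part suffices.** An early-pain difference alone could be reported as success on the primary endpoint of a trial whose hypothesis and size concern chronic pain. Testing each part at 0.05 would also exceed the 5% error.
- **Both parts are required.** The error rate is safe, but the trial's chance of success also depends on direct pain, for which nothing was planned.

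If the reading is settled only after results are known by arm, the choice itself can be driven by the results.

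**Working it through.** **Inputs.** From the Statistical analysis section: chronic pain 25% against 10%, α = 0.05, power 80%, 300 patients. From Surgical Techniques: equal allocation, so 150 per arm. Assumptions: two-sided tests (the article does not state the sidedness), and the correlations between test statistics used below.

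**1. The plan's own sample size.** With p̄ = (0.25 + 0.10)/2 = 0.175, the normal-approximation formula is

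n per arm = [z(1−α/2)·√(2p̄(1−p̄)) + z(power)·√(p₁(1−p₁) + p₂(1−p₂))]² / (p₁ − p₂)²

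The two roots are √0.28875 = 0.5374 and √0.2775 = 0.5268.

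n = [1.960 × 0.5374 + 0.8416 × 0.5268]² / 0.15² = 1.4965² / 0.0225 = 99.5, so 100 per arm and 200 in total (226 with continuity correction).

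The stated 300 is not reproduced. One-sided testing gives 158 (184 with continuity correction). The dropout step does reproduce: 300/0.95 = 315.8, so 316 = 2 × 158. The gap between 200 and 300 is a separate matter, but it is where the spare power in step 4 comes from.

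**2. Either part suffices, each tested at two-sided 0.05.** For k independent tests the chance of at least one false positive is 1 − 0.95^k. Correlated cases come from simulating 1,000,000 sets of equicorrelated normal test statistics.

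| Correlation (assumed) | Two outcomes | Three visits tested separately |
|---|---|---|
| 0 | 1 − 0.95² = 9.75% | 1 − 0.95³ = 14.3% |
| 0.5 | 9.1% | 12.5% |
| 0.7 | 8.4% | 10.9% |
| 0.8 | 7.8% | 9.9% |

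For two outcomes the sum of the two levels, 0.05 + 0.05 = 10%, bounds the error whatever the correlation. These rates count false claims in both directions. A false claim in favour of TIPP alone rises from 2.5% to at most about 1 − 0.975² = 4.9% under independence.

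**3. Both parts required.** The chance that both tests are falsely positive cannot exceed the chance for one, so the error is at most 5%.

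Power is the difficulty. Joint power cannot exceed the smaller of the two powers. For chronic pain with 150 per arm:

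Φ[(0.15·√150 − 1.960 × 0.5374)/0.5268] = Φ(1.488) = 93.2%

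For direct pain no rates are given, so its power cannot be computed. Joint power of 80% needs at least 80% power for direct pain. If the two tests were independent it would need 0.80/0.932 = 86%. Nothing in the article shows either.

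**4. Cost of splitting α.** At α = 0.025 for chronic pain, z = 2.241:

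- Power with 150 per arm: Φ[(1.8371 − 2.241 × 0.5374)/0.5268] = Φ(1.201) = 88.5%. Exact calculation gives 89.4% for the chi-square test and 86.2% for Fisher's test.
- Sample size for 80% power: [2.241 × 0.5374 + 0.8416 × 0.5268]²/0.0225 = 120.7, so 121 per arm and 242 in total (268 with continuity correction), below 300.

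**The case against.** The strongest reply is that no rule making success on either part sufficient is written down. The endpoint, the success statement under Study objectives and the Conclusion all join the two kinds of pain with a conjunction, which can be read as requiring both. On that reading nothing is inflated. Moreover, α appears only in the sample-size sentences, and no per-outcome or per-visit test is specified. This is a condensed article, and decision rules and testing order are commonly left to an analysis plan or full protocol, neither of which is shown.

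Most of this stands. The absence of a testing rule is not the point raised here. A reader might also infer that the error rate is in fact doubled or worse; the article does not support that. It needs the either-part rule, and about 10% is then the ceiling for two outcomes. The figure of about 14% needs each visit to be a separate primary test, whereas the article lists the visits only as times of data collection. It also assumes independence between pain reports from the same patients.

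What does not fall away is the mismatch that the article itself fixes: two outcomes in the primary endpoint, and one of them in the calculation. An analysis plan could add a decision rule. It could not make a power figure derived from chronic pain rates describe a two-part endpoint. The success statement does not settle the matter, since it sets an incidence threshold and does not compare the arms.

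**Conclusion.** The concern holds in conditional form. The primary endpoint contains two outcomes, while α, power and hypothesis were set for chronic pain.

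- If either outcome suffices at unadjusted 0.05, the family-wise error is up to about 10%, and about 8% to 9% at correlations of 0.8 to 0.5. It could reach about 14% only if all three visits were tested separately.
- If both outcomes must succeed, the error is not inflated, but the stated 80% does not describe the chance of success.

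The correlations and two-sided testing are assumptions. The adequacy of 300 patients is shown for chronic pain only; for direct pain it cannot be assessed from the article.

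**What to change.** State one decision in the Primary endpoint section, and align the abstract's Methods paragraph and the Statistical analysis section with it, before any outcome data are seen by arm.

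**Preferred.** Name chronic pain at one stated visit as the single primary endpoint, tested at two-sided 0.05. Test direct postoperative pain next, only if the primary result is significant. This fixed order keeps the family-wise error at 5% and matches the existing calculation. One year is a proposal, not something the article dictates; the sponsor must choose the visit. The cost is that direct pain loses stand-alone primary status.

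**Alternative.** Keep both as primary at 0.025 each, state that either may succeed, and say that the power figure applies to chronic pain only. The cost is some power for chronic pain: 88.5% instead of 93.2% with 150 per arm, still above 80%. Power for direct pain stays unknown until the sponsor supplies planning rates.

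Requiring both outcomes at 0.05 each is also valid and needs no split of α. It does need planning rates for direct pain and a joint power statement, so its sample size cannot be confirmed now.

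The first two options change wording only and add no patients to the chronic-pain comparison.
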